##### Fixed Variables

Fixed, or time-dependent variables that are hypothesized to be potential confounders will be used as additional covariates. This includes the subject's age and gender at inclusion, as well as their Body Mass Index (BMI) (see Table 1). Body weight is serially assessed at each occasion and if significant fluctuations are seen over time, the BMI may be added as a dynamic variable. In addition, the stroke type and side will be added. Lastly, the used equipment for serial subject-specific measurements will be evaluated as a potential confounder.

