##### Project B

After describing the recovery time course, we aim to investigate longitudinal associations between motor impairments in terms of leg muscle synergies (i.e., FMA-LE) and ankle strength (i.e., ankle item of the MI-LE) serving as independent variables, and the DCA which is the dependent variable. First, we analyze the pattern of neurological recovery following these clinical scales by using similar methods as outlined above. Second, we will apply a recently discussed hybrid model (64) to investigate longitudinal associations over the first 12 weeks poststroke. This method has the advantage of disentangling the between- and within-subject effects of this relation.

The between-subjects covariate score is determined as the individual average value over time of the independent variables which reveals the association irrespective of the development over time. On the other hand, the within-subject covariate is calculated as the observed value at each time point minus the individual average (i.e., deviation score). By this, we can estimate whether longitudinal changes of the dependent and independent variables within a subject are associated, i.e., are increasing scores on the FMA-LE or MI-LE ankle item related to changes following the DCA. Similar covariates will be entered in the model and tested on significance.

For all statistical tests, the likelihood ratio test will be used to examine the need to enter random effects into the model and the Wald test will be used to obtain *P*-values for regression coefficients in the final model. A 2-tailed significance level of 0.05 will be used for all analyses.

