### Sample Size Justification

To the best of our knowledge, this is the first study to prospectively investigate changes in the variables over time early after stroke. This certainly limits the effectiveness of a sample size determination based on a power analysis. Therefore, we determine and justify our sample size of *n* = 60 based on recruitment (2.2 participants/month) and drop-out (15%) rates as seen during the first year of recruitment. Considering that we will include not more than 3 to 4 (main) covariates in our random coefficient and hybrid models, we meet the “rule of thumb” saying that 10 subjects per variable are sufficient to perform bivariate and multivariate regression analyses.

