### Study Limitations

The study described in the current report also has some limitations. Although the number of participants that will be included in the current study is greater as compared to previous prospective balance recovery studies (30, 34, 40, 42, 68) [with ranges between *n* = 13 (68) and *n* = 37 (40)], the desired sample size is limited. Second, since we use one specific balance condition it is not possible to determine whether results can be generalized to other balance tasks. Recent literature suggests that increasing challenges may reduce the degree of asymmetry in bipedal balance control (74) and balancing in everyday life environments requires rather reactive control skills (11). The results may therefore not fully capture the upper boundary of neurological recovery at the hemiplegic side and translation to dynamic balance conditions remains unknown. However, incorporating more-challenging paradigms may lead to a greater amount of missing values since many subacute patients with hemiparesis are not able to safely withstand perturbations when standing (34, 42) or perform dynamic tasks such as walking (75) until several weeks after stroke. Third, repeated measurements were performed with either force-plates or a mobile pressure-plate system. This enables us to perform measures in various (clinical) settings and recruit more broadly. However, while both systems can extract bilateral COP profiles, technical variations differ. To control for this, focus lies on within-subjects time series analyses and, additionally, we will add “equipment” as a covariate to our regression models. Fourth, measurements are restricted to the first 12 weeks. Yet, it might be of interest to further continue measurements acknowledging that few studies revealed that about 15% of survivors improve (76) and 25% will deteriorate beyond the first 6 months (77). Lastly, the study did not monitor the type and amount of therapy provided to each participant and we are unable to correct for these factors. The lack of using uniform guidelines for stroke rehabilitation in Flanders, Belgium could lead to differences in how subjects are treated in cooperating facilities. Moreover, mildly-affected subjects may be discharged earlier and receive less intensive outpatient therapy afterwards. However, evidence that current rehabilitation interventions impact neurological recovery is still lacking so far (17, 78), particularly if provided as part of standard care which is shown to be low-dosed (79, 80). Since usual care has not been systematically modified, differences in rehabilitation treatment are expected to have a limited impact on outcomes of the current study.

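### Project B tests its hypothesised confounders for significance and does not say that they stay in; if non-significant ones are dropped, the between-subject coefficient can be biased at about 51 patients

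*Protocol article*

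**What the plan says.** All places are in the protocol article.

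- **Project A** names six covariates as potential confounders, most with a stated clinical or technical reason: gender, age, BMI, stroke side, stroke type and equipment. They are simply entered; no significance condition is attached.
- **Project B** carries them over with an extra step: "Similar covariates will be entered in the model and tested on significance". The section closes with "the Wald test will be used to obtain *P*-values for regression coefficients in the final model" and "A 2-tailed significance level of 0.05 will be used for all analyses".
- **Sample Size Justification** states that "we will include not more than 3 to 4 (main) covariates in our random coefficient and hybrid models", and supports this with a rule of ten subjects per variable.
- **Equipment** is described in several ways. Project A adds it. Fixed Variables says that "the used equipment for serial subject-specific measurements will be evaluated as a potential confounder". Study Limitations offers adding it "as a covariate to our regression models" as part of the control for device differences. Under Project B it falls among the covariates to be tested.

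**The concern.** A covariate's P-value against the outcome does not test confounding. Confounding depends also on how the covariate relates to the predictor, here a patient's mean FMA-LE or MI-LE ankle score. In a small sample a non-significant result says little about either link. If covariates chosen on clinical grounds leave the model because they miss 0.05, part of their effect passes into the between-subject coefficient. The Wald P-value then reported also ignores the selection.

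At stake is one of the two effects that the hybrid model was chosen to separate. An apparent between-patient association of motor impairment with dynamic control asymmetry (DCA) could partly reflect age, stroke type or measuring device.

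**Working it through.** **Inputs.** From the documents: n = 60 and 15% dropout ("we determine and justify our sample size of *n* = 60 based on recruitment (2.2 participants/month) and drop-out (15%) rates"), two-sided 0.05, six named confounders, three to four (main) covariates, ten subjects per variable. The documents give no device split, effect size or strength of confounding, so these are assumed and varied.

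**1. The plan's own arithmetic.** There is no power calculation to reproduce.
- Patients after dropout: 60 × 0.85 = 51.
- Rule of ten: 10 × 3 = 30 to 10 × 4 = 40. Both are below 51, so the rule holds for three to four variables.
- Six confounders plus the between and within terms make 8 variables. The rule would need 10 × 8 = 80 patients; 51 / 8 = 6.4 per variable (60 / 8 = 7.5).

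The full list therefore does not fit the rule. Something must be left out, or the limit must be restated, and significance is the only selection criterion in the text.

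**2. Chance that a two-group covariate such as equipment reaches significance.** Power ≈ Φ(d·√(n₁n₂/(n₁+n₂)) − 1.96), with d the difference in SD units. Example: d = 0.5 and 25.5 per group give 0.5 × √12.75 = 1.785, and Φ(−0.175) = 0.43.

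| d (SD) | 51 patients, 50/50 | 51 patients, 70/30 | 60 patients, 50/50 |
|---|---|---|---|
| 0.2 | 11% | 10% | 12% |
| 0.3 | 19% | 16% | 21% |
| 0.5 | 43% | 37% | 49% |
| 0.8 | 82% | 75% | 87% |

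A small or moderate confounder would be lost more often than kept. Patients who never stand for 30 s contribute no DCA, so the effective number may be below 51.

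**3. Effect on the between-subject coefficient.** Simulation at n = 51, 4,000 runs per setting, on subject means (the between part of a random-intercept hybrid model with balanced data). The true coefficient is zero and the residual SD is 1. There are six candidate covariates; r is a real confounder's correlation with the predictor and g its effect on the outcome. The first candidate is binary, coded ±1, so g = 0.25 is a 0.5 SD gap between groups. Backward elimination at 0.05 is compared with keeping all six.

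| Real confounders | r | g | First one kept | Bias, selection | Type I error, selection | Type I error, all six kept |
|---|---|---|---|---|---|---|
| 1 | 0 | 0.25 | 39% | 0.003 | 6.3% | 5.0% |
| 1 | 0.2 | 0.2 | 29% | 0.017 | 6.5% | 5.1% |
| 1 | 0.3 | 0.2 | 27% | 0.027 | 7.9% | 5.4% |
| 1 | 0.3 | 0.3 | 50% | 0.027 | 8.5% | 5.2% |
| 1 | 0.5 | 0.25 | 33% | 0.056 | 13.5% | 6.1% |
| 3 | 0.3 | 0.25 | 32% | 0.111 | 18.3% | 4.6% |
| 3 | 0.4 | 0.25 | 25% | 0.177 | 33.6% | 5.4% |

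The first row has no confounding, so its excess comes from selection alone. With all six kept, bias is within ±0.003 and the error stays near 5%; that test is exact in this set-up, so the spread is simulation noise. Separate runs of the same design gave 11.7-12.1% for two confounders (r = 0.3, g = 0.2 to 0.3) and 19.7% for three (r = 0.3, g = 0.25). When one of the three acts in the opposite direction, the error falls to 14.8%.

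**4. The within-subject coefficient.** This predictor is the observed score minus the patient's own mean. With complete data it is uncorrelated with anything constant within a patient. The Design section keeps each patient on the same equipment, so a device main effect cannot confound it. The protection is not perfect: DCA is missing until a patient can stand, and BMI may be entered as time-varying.

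**The case against.** **Removal is not stated.** A reader might infer that the plan deletes non-significant confounders. The text says only that they are entered and tested, and names no elimination procedure. The phrase "for regression coefficients in the final model" follows a clause about random effects, so it can mean the model after that decision. The word (main) in the covariate limit can refer to the terms of interest, since Fixed Variables calls the confounders additional. All of this stands, and backward elimination is therefore an assumption of the working. But if the limit does not cover the confounders, the rule of ten has not been applied to the model that will be fitted, and that too needs correcting.

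**Equipment.** A reader might infer that equipment will be dropped. Project A and Study Limitations say that it is added, and no section says that it may leave. DCA is a ratio, so a pure scale difference between devices cancels; noise added to the velocity of both legs would not, and would pull the index toward zero. No section links device to FMA-LE or MI-LE. What stands is that the four descriptions need to agree.

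**The coefficient affected.** The Objectives ask about longitudinal association, which is the within-subject term. That is correct and limits the harm.

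**Detail left to a fuller plan.** Retention rules are often given there. Here, however, the article states a rule, and the rule as worded invites selection by P-value.

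**Conclusion.** The point holds as a fault in a stated rule whose consequence is conditional. Testing hypothesised confounders for significance, with six named and three to four allowed, most naturally permits dropping them. At about 51 patients such screening has low power to keep small or moderate confounders.

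If it is applied, the type I error of the between-subject coefficient is about 6-8% under weak confounding, and 10-20% or more with several moderate confounders in the same direction. The size rests on assumed correlations and effects and on backward elimination at 0.05. A single figure in the upper part of that range should not be read as the expected error rate of this study.

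A reader might also infer that the longitudinal conclusion of Project B is unsafe. The documents do not support that: time-fixed covariates leave the within-subject coefficient largely untouched.

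**What to change.** - Name in advance, on subject-matter grounds, the Project B covariates that stay in every model whatever their P-values. Include equipment, as Project A and Study Limitations already say. Covariate P-values may be reported but should not decide retention.
- Reconcile that list with Sample Size Justification in one of two ways. Either choose a smaller set now: 51 / 10 = 5.1 allows five variables, that is the between and within terms plus three covariates. Or keep all six and restate the limit, acknowledging about 6.4 subjects per variable.
- Say what (main) covers, and bring Fixed Variables, Project A, Project B, Sample Size Justification and Study Limitations into line.

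The cost is wording in the analysis plan, and slightly wider intervals where a retained covariate proves unrelated to the outcome. No data collection changes.

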### Sample Size Justification

To the best of our knowledge, this is the first study to prospectively investigate changes in the variables over time early after stroke. This certainly limits the effectiveness of a sample size determination based on a power analysis. Therefore, we determine and justify our sample size of *n* = 60 based on recruitment (2.2 participants/month) and drop-out (15%) rates as seen during the first year of recruitment. Considering that we will include not more than 3 to 4 (main) covariates in our random coefficient and hybrid models, we meet the “rule of thumb” saying that 10 subjects per variable are sufficient to perform bivariate and multivariate regression analyses.

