### Participants

In total, this study will include a cohort of 60 patients after a first-ever hemispheric stroke of ischemic or hemorrhagic cause within, at most, 3 years of recruitment. This cohort will be recruited from the stroke units at the University Hospital Antwerp (Edegem, Antwerp, Belgium), the GZA Hospital campus St Augustinus (Wilrijk, Antwerp, Belgium) and the General Hospital Geel (Antwerp, Belgium). All cooperating hospitals are located in the larger Antwerp region in Flanders, Belgium. Stroke survivors will be screened and asked to participate as soon as possible and within the first 3 weeks after stroke onset. Only survivors who are, or will be admitted to one of the involved rehabilitation facilities (RevArte, Edegem, Antwerp, Belgium or the rehabilitation hospital Geel, Geel, Antwerp, Belgium) for inpatient treatment (eventually followed by outpatient treatment) are considered for inclusion, as the repeated measurements will be performed there. In addition, ten middle-aged (i.e., 45 to 65 years) healthy adults (gender equally distributed) with no known musculoskeletal or neurological injury or illness that may affect balance control will be recruited to serve as controls for the interpretation of posturographic measures of quiet stance balance control.

Before entry, an information brochure about the study's aim, content and potential risks, together with information about the investigators is provided to each prospective subject (and if adequate to her/his family). If the subject feels sufficiently informed and agrees to participate, an informed consent is signed and eligibility is determined according to the following criteria.

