#### Statistical Analysis

##### Project A

In project A, we aim to investigate time-dependent changes in metrics of quiet stance balance control. To estimate how each parameter is changing as a function of time poststroke, we use a random coefficient analysis (or mixed model analysis) with “time” of measurements as the main fixed effect (JMP Pro, version 15). Additionally, “time” will be entered as an independent covariate in form of an subject-specific slope (i.e., the interaction term “participant^*^time”) to adjust for dependency of repeated observations. However, the greatest advantage of this method is its flexibility in dealing with missing values. The latter may result from subjects being unable to stand at first occasions, being unavailable due to hospital discharge or transfers, or by no longer corresponding to eligibility criteria for example due to a recurrent stroke or other sudden medical condition (potentially) affecting outcome variables. Moreover, the value on the addressed metric at 3 weeks poststroke will be added to account for inter-subjects variability.

In addition, fixed covariates that are hypothesized to be potential confounders will be entered in the model. This includes “gender,” “age” and “BMI” considering their influence on standing balance control. [i.e., females and elderly tend to show greater body sway (60) and obesity is associated with instability (61)]. Second, stroke “side” and “type” will be added, as right-sided lesions typically result in greater balance deficits (62) and subjects with hemorrhagic strokes may display delayed recovery (63). Lastly, “equipment” is added as a potential confounder considering technical variations in measuring instruments.

Statistical analysis of the difference in each measure of quiet stance balance control between subjects and healthy controls will be performed using the Mann-Whitney U test for each measuring system separately.

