### Trial Status

Participant recruitment began in January 2019 in the University Hospital Antwerp and the RevArte rehabilitation hospital, in the GZA Sint-Augustinus hospital in April 2019 with a temporal suspension of recruitment in all involved sites between March and September 2020 due to Covid-19 measures. In response, an additional partnership with the General Hospital Geel in January 2021 was set-up. By now (October 2021), 52 stroke survivors were recruited indicating feasibility of reaching the desired sample size within the proposed recruitment period.

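### The 10-subjects-per-variable rule is declared met for 3 to 4 covariates, but the Project A model as listed has at least 8 fixed terms, or 7.5 patients per variable with 60

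*Protocol article*

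**What the plan says.** The Sample Size Justification says that a power analysis would be of limited use here. It sets n = 60 "based on recruitment (2.2 participants/month) and drop-out (15%) rates as seen during the first year of recruitment" and then adds one statistical argument, a rule of thumb of 10 subjects per variable for regression. It says the rule is met, giving as the reason: "Considering that we will include not more than 3 to 4 (main) covariates in our random coefficient and hybrid models".

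The models are described in the Statistical Analysis section:

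- **Project A.** Time is the main fixed effect, and the 3-week value of the outcome is added. Then "fixed covariates that are hypothesized to be potential confounders will be entered in the model". The confounders named are gender, age, BMI, stroke side, stroke type and equipment. The Fixed Variables section lists the same six, for instance "In addition, the stroke type and side will be added".
- **Project B.** Each impairment measure (FMA-LE and the MI-LE ankle item) is split into a between-subject average and a within-subject deviation. On adjustment the section says: "Similar covariates will be entered in the model and tested on significance".

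**The concern.** The sample size section counts 3 to 4 covariates, while the analysis sections enter about twice as many terms. The rule of thumb is the only statistical, as opposed to logistical, support offered for n = 60. If the count behind it does not match the models, a reader is told that the models have a property they lack. The reader also cannot tell which covariates the final models are meant to contain, and that leaves room to choose them after seeing the data.

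**Working it through.** **Inputs from the protocol article**

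- Patients: 60 (Participants: "this study will include a cohort of 60 patients after a first-ever hemispheric stroke"). This is a recruitment target, since Trial Status measures recruited patients against it: "By now (October 2021), 52 stroke survivors were recruited indicating feasibility of reaching the desired sample size".
- Drop-out: 15% (Sample Size Justification).
- Rule: 10 subjects per variable, so required N = 10 × k and the permitted k = N / 10.

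**Step 1: the plan's own claim.** With k = 3 to 4 the rule asks for 30 to 40 patients.

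- 60 patients: 60/3 = 20 and 60/4 = 15 per variable.
- 51 patients (60 × 0.85): 51/3 = 17 and 51/4 = 12.75 per variable.

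With 3 to 4 variables the claim is right under either denominator.

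**Step 2: terms in the models as described**

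| Model | Terms | k |
|---|---|---|
| Project A, time linear | time 1 + 3-week value 1 + six confounders | 8 |
| Project A, time categorical (4 occasions) | time 3 + 3-week value 1 + six confounders | 10 |
| Project B, one scale per model | between 1 + within 1 + six confounders | 8 |
| Project B, both scales together | between 2 + within 2 + six confounders | 10 |

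Only the first row follows directly from the text. The second assumes categorical time, which is not stated. The Project B rows assume that similar covariates means the same six. Adding time to the hybrid model would raise those rows further.

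**Step 3: the rule applied to those counts**

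| k | Required (10 × k) | 60/k | 51/k |
|---|---|---|---|
| 6 (confounders only) | 60 | 10.0 | 8.5 |
| 8 | 80 | 7.5 | 6.4 |
| 10 | 100 | 6.0 | 5.1 |

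The largest k that the rule permits is 60/10 = 6 with all patients, and 51/10 = 5.1, so 5, after drop-out. At 8 terms the rule fails with all 60 patients counted, so the result does not depend on drop-out.

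**The case against.** The strongest reply is that the word in brackets, main, was chosen on purpose. The Outcomes section treats the impairment scales as the main independent variables and calls the demographic, lesion and equipment variables additional covariates. Two scales split into between and within terms make exactly four. On this reading the count is correct but covers only the main terms. The reading is possible, but it does not rescue the conclusion: the rule as cited counts variables and makes no exception for adjustment variables.

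A second reply is that the covariates are candidates and only 3 to 4 would survive. This has some support in Project B, where they are tested on significance and a final model is mentioned. Project A describes no reduction step. In Project B no retention rule or cap is given, and candidates that are entered and then tested still count towards the rule.

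Two further replies limit the size of the point. A mixed model keeps the data of patients who leave after one or more assessments, so 51 is a pessimistic denominator. Each patient also gives up to four measurements, which inform the time and within-subject terms; the plan's rule, however, counts subjects. On the other side, patients who cannot stand at 3 weeks have no 3-week posturographic value, but the article does not say how many there will be.

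A reader might infer that 60 patients are too few, or that the estimates will be unstable and the intervals too narrow. The article does not support that. It gives no effect size, standard deviation or power, and no calculation here shows such harm. A ratio of 5 to 6 per variable should not be the headline either: 5.1 needs both 10 terms and drop-outs who contribute nothing, and 6.0 needs 10 terms.

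**Conclusion.** The point holds as an inconsistency between the sample size section and the models. For Project A as listed (8 fixed terms, time linear) the ratio is 7.5 patients per variable with 60, and 6.4 if all drop-outs contribute no data, against a stated minimum of 10. For Project B the same figures apply with one scale per model, provided the same six covariates are used; with both scales jointly they are 6.0 and 5.1. The statement that the rule is met is therefore wrong for the models as written.

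This should be corrected, but it does not undermine the study. The rule is secondary support in an observational cohort that disclaims a power analysis, names its limited sample size as a limitation, and had already recruited 52 of 60. Whether 60 is adequate by a power criterion remains open.

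**What to change.** Preferred: in the Sample Size Justification, say what the word main covers, give the actual number of fixed terms in each model and the resulting patients per variable (about 7.5 at 8 terms with 60, 6.4 with 51), and remove the claim that the rule is met.

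Alternative: prespecify for each project a primary model whose total fixed terms stay within the rule, at most 6 counting on 60 patients or 5 counting on 51. The total must include time, the 3-week value and the between and within scores. In Project A, linear time and the 3-week value leave room for 6 − 2 = 4 confounders (or 5 − 2 = 3). In Project B, before any time term, one scale leaves 4 (or 3), and both scales jointly leave 6 − 4 = 2 (or 5 − 4 = 1). Keep the chosen set regardless of p-values and report the fully adjusted model as a sensitivity analysis.

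Cost: the first option is a rewording with a less favourable stated figure. The second puts fewer confounders in the primary model. Neither needs more patients.
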